### Participant reported outcomes

Patient focused outcomes will be recorded pre-randomisation at the baseline visit and on an annual postal or online follow-up questionnaire until 3-years post-randomisation (except when indicated otherwise).

Dental pain and need for dental pain relief will be recorded on the annual patient questionnaire. Dental pain will be measured using a Numerical Pain Rating Scale (NPRS) [24]. Health status will be assessed using the generic EQ-5D-5L, consisting of five dimensions of Health-Related Quality of Life (HRQoL) [25]. Oral Health Related Quality of Life will be assessed using the Oral Health Impact Profile 14 (OHIP-14). OHIP-14 is the most commonly used validated oral HRQoL measure and has been used successfully in previous HTA trials [26]. Oral Health behaviours will be assessed at baseline and 3-years post-randomisation using questions about type of toothbrush, brushing twice a day for 2 min, frequency of interdental cleaning and behaviour after brushing.

### Outcomes from data linkage with routine administrative NHS health records

Dataset: Management Information and Dental Accounting System (MIDAS) [27] collated information on all child and adult primary care dental practice appointments and treatments in Scotland (including Childsmile practice prevention items)**.**

Trial participant data will be linked to individual health records from MIDAS database, tooth-specific data on specific treatments (restorations, root canal therapy, and extractions).

### Economic outcomes

NHS perspective costs will be collected using a combination of clinician reported data using CRFs (for the costs of intervention delivery and caries treatment provided), data linkage to routinely collected dental claims (including tooth level data where possible) from the respective countries (ISD in Scotland, NHS BSA in England) and participant reported contact with non-dental NHS services for problems related to their teeth. Participant perspective costs will be obtained from NHS claims data (for treatment co-charges) and through self-reported information through participant completed questionnaires in practice and annually. Time, travel and lost productivity costs associated with required dental care will be collected through a questionnaire with a sample of respondents, collected in the first or second annual questionnaire. EQ-5D-5L data from annual questionnaires will be used to calculate QALYs.

General population preferences will be obtained from a discrete choice experiment (DCE with an online representative sample of the UK general population. The DCE will be used to elicit willingness to pay (WTP) for SCR, CCR and patient relevant short and longer term outcomes (e.g. need for further treatment). The DCE will be used to predict intervention uptake.

### Process evaluation

A mixed-method process evaluation will complement the outcome evaluation and examine implementation, mechanisms of impact and context as per MRC guidance [25]:

#### Implementation

The process through which the intervention (SCR or CCR) is delivered in dental practices, what is delivered in different practices and by whom, the fidelity and adaptation of the protocol and the resources used.

#### Mechanisms of impact

How the intervention is received by patients (acceptability) and how clinician/patient interactions trigger change in approaches to caries removal and placement of restorations and any unintended effects.

#### Context

Through examining how external factors including dental contracts and the use of skill mix influence the delivery of the intervention and its outcomes. The process evaluation will include the self-report questionnaires as described above, analysis of trial outcomes data (including CRFs) and qualitative interviews with patients, dental professionals and other stakeholders such as managers of corporate bodies and dental service commissioners.

### Process evaluation: qualitative interviews—SCRiPT participants

A sample of SCRiPT participants will be interviewed to explore their experiences of the intervention. A purposive sample will be used to ensure a range of participants in terms of age, patterns of dental attendance and tooth vitality or not. Potential participants for interview will be identified by the research team and they will be sent a letter of invitation along with a participant information sheet about the interview. Those who are willing to take part in the interview will return an expression of interest form to the research team. If they expressed an interest in being interviewed, they will then be contacted by the researcher to arrange a suitable time and location to hold the interview. Before the start of each interview the researcher will obtain informed consent. Recruitment will continue until no new themes emerge. Previous similar studies have involved 10–15 patients in qualitative interviews [25]. The interviews will be guided by the concept of patient acceptability using a topic guide developed by the research team. The interviews will be audio-recorded and transcribed verbatim by a professional transcription service who will be approved as vendors by the sponsor. The data will be analysed using framework analysis as it provides a pragmatic approach which produces results that can be easily incorporated into mixed-method studies, process evaluations and RCTs [28–30] (see details below).

### Process evaluation: qualitative interviews—dental stakeholders

A sample of dental stakeholders will be interviewed during the set-up phase to explore their views about the usual care they provide and how they envisage delivering the intervention, and during the trial to explore their experiences of delivering the intervention within their own setting. Individual stakeholders may take part in one or two interviews and may be interviewed at both time points to consider experiences of the trial in relation to expectations. Dental stakeholders will be purposively sampled based on role, geographical location, the types of dental contract they are working under, previous experience of differing restorative techniques and, for interviews carried out once sites have opened, their levels of engagement with the trial. Potential stakeholder participants will be selected, with dental professionals selected from the list of all practices involved in SCRiPT. The sample will include those who had recorded instances of having deviated from the clinical protocol for a variety of reasons, as these cases are of particular interest. Recruitment will continue until no new themes emerge. Previous similar studies have involved 25–30 stakeholders in qualitative interviews [31]. Potential participants for interview will be identified by the research team and they will be sent a letter of invitation along with a participant information sheet about the interviews. Before the start of each stakeholder’s first and any subsequent interview the researcher will obtain and record informed consent using appropriate method, e.g. verbal, written, digital.

The interviews will be guided by the theoretical domains framework (TDF) [32] which has been used previously in implementation research to understand the motivations, cognitions and behaviours of dental professionals when implementing evidence-based practice [31–33]. A topic guide based on the TDF has been developed by the research team. The interviews will be audio-recorded and transcribed verbatim by a professional transcription service who will be approved as vendors by the sponsor. Framework analysis based on the TDF will be used.

The analysis will involve the following stages: identifying initial themes, labelling the data, sorting the data by theme and synthesising the data. The analysis will be conducted by an experienced research associate with support from grant-holders. In addition, during the analysis, regular meetings will be held between the research team to discuss the emergent themes and consider the implications of these for the implementation and delivery of the intervention.

### Scheduling of events

Data will be collected as detailed in Table 1.

**Table 1 Tab1:** Scheduling of events

	Screening	Baseline (initial treatment visit)	At time of intervention/dental visits	Annual Questionnaire	36 months	Other
Assessment for eligibility	o					
Informed consent		o				
Socio-demographic characteristics and eligibility for free treatment		o				
Clinical status (DMFT)		o				
Sustained tooth vitality			o		o	o
Pulp exposure during caries removal			o			
Caries progression dental pain relief			o		o	o
EQ-5D-5L		●		●	●	
OHIP-14		●		●	●	
Patient satisfaction				•	●	
Oral health behaviours		●			●	
NHS perspective primary dental care resource use and cost			o			∇
NHS perspective use of other NHS services (GP, A&E etc.)			o	●	●	
Patient perspective unit costs of time and travel^A^				●		
Patient perspective costs (private care, NHS co-charges etc.)				●	●	∇
General population preferences						⊕
Willingness to pay						⊕

^A^Costs of time and travel will be collected from a randomly selected subset of participants, across the different annual questionnaire time-points. Each selected participant will complete the questions once only

o: Dental Practice-CRF

●: Questionnaire

∇: Data linkage to routine administrative datasets, ongoing over trial duration, at the end of the study, and for longer term follow-up

⊕ DCE, administered once online to a nationally representative sample of the UK general population

## Study within a trial

Poor retention of participants recruited to clinical trials is a known problem which can reduce statistical power, bias estimates of intervention effects and reduce the credibility of trial results [34]. SCRiPT will investigate whether giving participants a welcome letter on entry to the trial improves questionnaire response rates and retention across the trial’s follow-up. The letter will welcome participants to the trial, reiterate the participant journey (summarising information provided in the patient information leaflet), identify the location of the participant’s study tooth and list the expectations for participation i.e. the need to return the trial questionnaires. Allocation to receive or not receive the letter will be randomised following recruitment into the trial by the trial office and will be 1:1. The intervention group will be issued with a letter within 2 months of consent to participate. The control group will not be issued with a letter.

## Analysis plan

### Sample size calculation

The sample size calculation is event-based. We aim to detect an absolute improvement in sustained tooth vitality at three years of 12% from 80% (CCR) to 92% (SCR). The control rate of 80% is based upon the existing evidence base, clinical experience and confirmed by Scottish tooth-level routine data. As described in Sect. 2.1 above, the current evidence base gives rates of pulpal exposure that are higher than those seen in UK NHS and therefore our rate of sustained tooth vitality will be higher than observed in those studies. Bjørndal 2017 [12] presented a tooth vitality rate of approximately 80% at 3 years for two-step selective restoration in lesions that were deeper than those in this trial. The two-step procedure is more similar to a CCR than the SCR in our trial. The Scottish tooth specific data demonstrated that of 459,648 teeth that required a three surface restoration in 2013, 6.6% had received further endodontic treatment or were extracted at 3 years follow-up. These teeth however, could be at any level of dentine involvement and it is not possible to identify the level of involvement in the routine data. Therefore, as the study is interested in only teeth with involvement in the pulpal third of dentine, it has been estimated that the number of events may be three times larger. There is little empirical evidence to inform the expected size of an important effect. A target difference of 12% was judged clinically important and plausible by both dentists and PPI partners. The target difference of 12% was also informed by the difference observed in Bjørndal 2017 [12] which was 13.7% at 5 years. However, as this is a patient RCT there are concerns around contamination (participants receive the intervention that they were not randomly allocated to). The team conservatively have allowed for up to 25% contamination and therefore the sample size for SCRiPT aims to detect an absolute improvement of 9%; from 83 to 92% at three years. Recruitment of 623 participants (71 events) will detect a hazard ratio of 0.42 between experimental and control strategies and provide, using the log-rank test, assuming an exponential failure rate, 90% power at a 2-sided 5% significance level. The calculation also assumes 17 months of recruitment, a minimum of 33 months of follow-up and a 30% follow-up attrition at the end of year three. Recruitment is assumed to be staggered and builds in seasonal variation. We used the Stata package ARTSURV for calculations [35].

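### The stated detectable hazard ratio of 0.42 should be about 0.45; the 71 events, 623 participants and 90% power fit 0.45 and can stand

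*Protocol article*

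**What the plan says.** All the inputs are in the Protocol article, section Sample size calculation. The target before contamination is three-year vitality of 80% on complete caries removal and 92% on selective caries removal. The section then makes an allowance for crossover: "The team conservatively have allowed for up to 25% contamination". After this the design "aims to detect an absolute improvement of 9%; from 83 to 92% at three years".

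The result is given as: "Recruitment of 623 participants (71 events) will detect a hazard ratio of 0.42 between experimental and control strategies". The conditions attached are "using the log-rank test, assuming an exponential failure rate, 90% power at a 2-sided 5% significance level", together with "17 months of recruitment, a minimum of 33 months of follow-up and a 30% follow-up attrition at the end of year three". On the pattern of entry the section says only: "Recruitment is assumed to be staggered and builds in seasonal variation". The software is named ("We used the Stata package ARTSURV for calculations"), but its input is not shown. No other section derives or restates the hazard ratio.

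**The concern.** Two survival proportions at the same time point, under exponential failure, fix one hazard ratio. The section gives the two proportions and the exponential assumption, so its hazard ratio can be checked directly, and it does not agree with them.

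The hazard ratio is the scale of the primary analysis: the section Primary outcome, under Analysis plan, specifies a Cox model and reports the treatment effect as a hazard ratio with a 95% confidence interval. A wrong design value on that scale misstates the effect for which the trial was sized. Anyone who repeats the calculation from the printed value will obtain a different event target or a different power. The question is how far the error reaches: whether it touches only the printed hazard ratio, or also the event count, the power or the number of participants.

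**Working it through.** **Inputs** (all from Sample size calculation, except 1:1 allocation from Identifying and recruiting participants): 83% and 92% at 36 months; 623 participants; 71 events; log-rank test; two-sided 5%; 90% power; 17 months of recruitment; at least 33 months of follow-up; 30% attrition at year three.

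**Step 1: where 83% comes from.** 0.75 × 80% + 0.25 × 92% = 60% + 23% = 83%. The article does not spell out this step, but it reproduces the 83% exactly and leaves a difference of exactly 9 points.

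**Step 2: candidates for the printed 0.42.**
- Hazard ratio, 83% v 92%: ln(0.92)/ln(0.83) = 0.4475
- Odds ratio, 83% v 92%: (0.08/0.92)/(0.17/0.83) = 0.4246
- Risk ratio, 83% v 92%: 0.08/0.17 = 0.471
- Hazard ratio, 80% v 92%: ln(0.92)/ln(0.80) = 0.374

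Only the odds ratio rounds to 0.42.

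**Step 3: events needed for 90% power.** With z = 1.960 + 1.2816, Schoenfeld's formula is 4z²/(ln HR)² and Freedman's is z²[(1 + HR)/(1 − HR)]². Power with 71 events is Φ(√71·|ln HR|/2 − 1.960) and Φ(√71·(1 − HR)/(1 + HR) − 1.960) respectively.

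| Hazard ratio | Events needed (Schoenfeld / Freedman) | Power with 71 events (Schoenfeld / Freedman) |
|---|---|---|
| 0.42 | 55.8 / 63.0 | 95.5% / 93.1% |
| 0.4475 | 65.0 / 72.1 | 92.3% / 89.5% |

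Run the other way, 71 events at 90% power correspond to a hazard ratio of 0.463 (Schoenfeld) or 0.444 (Freedman). The printed 0.42 lies outside this range and 0.4475 inside it.

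**Step 4: do 623 participants and 71 events follow from 83% v 92%?** Monthly hazards are −ln(0.83)/36 and −ln(0.92)/36, with exponential loss at −ln(0.70)/36. Follow-up runs from 33 to 50 months (33 + 17) according to entry date. The log-rank expectation and variance were integrated numerically. Because the accrual pattern is not given, three were assumed: uniform, and entry distributions (x/17)^1.5 and (x/17)² for moderate and strong back-loading.

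| Hazard ratio | Accrual (assumed) | Expected events, N = 623 | Power, N = 623 | N for 90% power | Events for 90% power |
|---|---|---|---|---|---|
| 0.4475 | uniform | 73.0 | 90.9% | 604 | 70.7 |
| 0.4475 | moderately back-loaded | 70.8 | 90.0% | 623 | 70.8 |
| 0.4475 | strongly back-loaded | 69.3 | 89.4% | 636 | 70.8 |
| 0.42 | uniform | 71.6 | 93.8% | 536 | 61.6 |
| 0.42 | moderately back-loaded | 69.5 | 93.1% | 553 | 61.6 |
| 0.42 | strongly back-loaded | 68.0 | 92.6% | 565 | 61.7 |

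These figures use the local-alternative variance. The distant-alternative version raises the events needed slightly, to 71.3 at 0.4475 and 62.2 at 0.42.

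At 0.4475 the printed 623, 71 and 90% are recovered together under a plausible back-loaded pattern. At 0.42 none of the three patterns does this.

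**The case against.** **Rounding.** If both percentages were rounded to whole numbers, the hazard ratio could lie anywhere from 0.405 to 0.493. Also, 0.83^0.42 = 0.9247, which would print as 92%. This is the best defence of 0.42, but it fails on two counts. The 83% is the exact mixture of 80% and 92%, and the difference is stated as 9 points, whereas 92.47% would make it about 9.5. And rounding cannot make 0.42 agree with 71 events at 90% power.

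**Event accrual.** With 623 participants and uniform entry, 0.42 would itself produce about 71.6 events, so the pairing of 623 with 71 does not alone separate the two values. The power does: it would be 93.8%, and only 536 participants would be needed for 90%.

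**Sidedness and length of follow-up.** A one-sided test needs fewer events still at 0.42 (46 to 52). Capping follow-up at 36 months leaves the need at about 62 events.

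**Consequence.** It is fair to say that little depends on the figure. The target is justified on the absolute scale, the correct rates stand beside it, no interim analysis of outcomes is planned, and no section compares the estimated hazard ratio with a design value. The slip also errs on the cautious side, because it makes the detectable effect look larger than it is. This limits the severity but does not make the number right.

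**Stronger readings the documents do not support.** A reader might infer that the event count and power are also wrong and should become about 73 events and 91%. Those values follow only from uniform accrual, while the section says entry is staggered and seasonal. A reader might also take it as established that an odds ratio was printed as a hazard ratio. The match is close, but the article does not state the source.

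**Conclusion.** The point holds for one number. Under the section's own exponential assumption, 83% v 92% is a hazard ratio of 0.447, and the printed 0.42 is too low by about 0.03. Taken literally, 0.42 describes about 82% v 92%, since 0.92^(1/0.42) = 0.820, or 83% v 92.5%. It conflicts with the 71 events and 90% power in the same sentence, needing only about 56 to 63 events or giving about 93% to 95.5% power.

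The 623 participants, 71 events and 90% power are consistent with 0.447 and need not change. That conclusion assumes exponential loss reaching 30% at 36 months and follow-up continuing to a common end date (33 to 50 months). The exact agreement at 623 also depends on an assumed accrual pattern. The hazard ratio itself depends on none of these, only on the two rates and the exponential assumption. Severity is low: a stated design figure is wrong, with no effect on recruitment or on the planned analysis.

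**What to change.** In Sample size calculation, replace the hazard ratio of 0.42 with a hazard ratio of 0.45 (83% v 92% at three years). Keep 623 participants, 71 events and 90% power. Before doing so, rerun ARTSURV at a hazard ratio of 0.447 with the trial's own staggered, seasonal accrual pattern to confirm those three figures. If 0.42 came from some other calculation, state its derivation. Wherever else the design hazard ratio is quoted, use the same corrected value. The cost is one sentence and one rerun of an existing calculation.

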
### Proposed analyses

Demographic and baseline characteristics will be summarised and displayed in tables for all randomised patient participants using appropriate summary statistics. All analyses will initially be performed on an intention -to-treat basis, although use causal methods for the analysis of the primary outcome to estimate efficacy in the presence of cross- over between treatment arms will also be used. Analysis will be fully specified in a Statistical Analysis Plan.

### Primary outcome

The primary endpoint, sustained tooth vitality, will be analysed within a time-to-event framework using a Cox proportional hazards model, adjusted for minimisation covariates and a random effect for clinician included. The treatment effect will be summarised by the hazard ratio with a 95% confidence interval. The estimated survivor function will be graphed.

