### Monitoring fidelity to protocol

Monitoring fidelity with the clinical protocol is essential to exclude merger of the clinical techniques and consistency of technology used when more than one tooth has a deep carious lesion. We will implement 3 strategies to assess compliance:Clinicians will be asked after every third patient to cut both a SCR and CCR cavity in two 3D computer generated sample teeth and return these to the research office. These teeth will be examined by a member of the clinical team to monitor compliance. If merger of SCR and CCR is observed additional training and or reinforcement of protocol will be providedThe CRF will include an assessment of colour, hardness and consistency to monitor whether SCR or CCR has been performed according to protocol. The lighter shade would be consistent with CCR, a darker shade with SCR. The hardness of the cavity will be assessed with a dental explorer/spoon excavator. Soft would indicate SCR and hard would indicate CCR. The CRFs will be assessed in real time to monitor fidelity and feedback will be provided if evidence of merger is observed.Baseline and 1-year follow-up bitewing radiographs will be assessed by a researcher masked to treatment group, to confirm the extent of initial caries and following the restoration the presence of caries. Follow up x-rays will be taken at intervals judged appropriate by the clinicians therefore assessment will be 6–12 months after treatment.

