#### Identifying and recruiting participants

The trial will aim to recruit 65 practices (each recruiting an average of 10 participants) to achieve the target of 623 participants. Trial clinicians will identify patients at routine visits that meet the inclusion criteria and explain the trial. Eligible patients who express interest will be given a participant information leaflet (Additional file 1) and an appointment for their treatment as per current clinical practice. At the treatment visit the patient will be given the opportunity to clarify any questions prior to informed consent being obtained and recorded on a written consent form (Additional file 2).

The eligibility of all participants will be assessed and determined by their dental practitioner following clinical and radiographic examination according to pre-determined criteria. Those who do not wish to take part will receive caries removal and restoration as per current practice. Those who are eligible and wish to take part will give informed consent to the clinician providing treatment.

A baseline questionnaire will be completed by the participant to collect baseline patient centered outcomes. Randomisation will then take place using an online randomisation system. If the participant has more than one eligible tooth, a trial tooth will be selected at random by the randomisation application. The randomisation algorithm will use recruitment site, number of eligible teeth (1; > 1) and type of caries (primary and secondary) as minimisation covariates to allocate to treatment intervention and control groups in a ratio of 1:1To maintain participant blinding, participants will not be informed of their allocated treatment group following randomisation. Baseline clinical information will be recorded by the clinician after the treatment has been provided.

After the initial intervention participants will receive any treatment deemed clinically appropriate by their dentist as per normal practice.

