### Baseline characteristics

At baseline information will be collected on participants’ socio-demographic characteristics, generic health-related quality of life, oral health-related quality of life, oral health behaviours, and time and travel costs through a participant questionnaire. Oral health status and caries experience (DMFT) will be calculated by the clinician. Bitewing radiographs and periapical radiographs (if clinically needed) will be collected as part of routine care but copies will be provided to the trial team to provide a measure of the extent of caries and confirm exclusion of signs of pulp pathology. A case report form (CRF) will record the details of treatment including caries removal, restoration placed, and resources required to deliver the respective treatments. Any modification of or deviation from the intervention will be recorded on the CRF to inform the clinical outcomes.

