### Planned subgroup analysis

Subgroup analyses on the primary outcome will explore the possible modification of treatment effect by age and number of lesions. This will be done by including treatment-by-factor interactions in the model and they will be classified as exploratory analyses.

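### The primary and pulp-exposure models name only the minimisation covariates; prespecifying age and the masked baseline-film reading of caries extent would be a cheap, modest and optional efficiency gain

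*Protocol article*

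**What the plan says.** Under Analysis plan, Primary outcome, the time-to-event model is a Cox model "adjusted for minimisation covariates and a random effect for clinician included". Under Analysis plan, Secondary outcomes, pulp exposure gets a logistic regression with the same adjustment. Identifying and recruiting participants defines the set: "recruitment site, number of eligible teeth (1; > 1) and type of caries (primary and secondary) as minimisation covariates".

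Two other pre-treatment variables are available.

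- **Caries extent.** Radiographs come from routine care and "copies will be provided to the trial team to provide a measure of the extent of caries" (Baseline characteristics). Monitoring fidelity to protocol adds that "Baseline and 1-year follow-up bitewing radiographs will be assessed by a researcher masked to treatment group, to confirm the extent of initial caries".
- **Age.** The article states that "At baseline information will be collected on participants’ socio-demographic characteristics". Age is not named in that sentence, but it is an inclusion criterion, and the planned subgroup analysis will "explore the possible modification of treatment effect by age and number of lesions", so it must be recorded.

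Depth also enters the sample size argument. A three-year failure rate of 6.6% in routine data, covering teeth of every depth, is scaled up for pulpal-third lesions: "it has been estimated that the number of events may be three times larger". Proposed analyses leaves the full specification to a statistical analysis plan.

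**The concern.** Where a baseline variable predicts failure, leaving it out of a Cox model loses some power. The treatment coefficient is drawn towards zero while its standard error hardly changes. With only about 71 events planned, even a small gain is worth having if it needs no new data.

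Pulp exposure happens while caries is being removed, so lesion depth may plausibly matter at least as much there. The article gives nothing from which to size that effect.

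Timing matters too. Covariates written in before outcomes are seen raise no questions, whereas the same covariates added afterwards invite a charge of selective adjustment.

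**Working it through.** **1. Inputs** (Sample size calculation): 623 participants, 71 events, 83% v 92% vital at three years after the contamination allowance, two-sided 5%, 90% power, exponential failure, 17 months of recruitment, at least 33 months of follow-up, and 30% attrition by year three. Allocation is 1:1.

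**2. Reproducing the plan's figures.**

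- Hazard ratio implied by 83% v 92% under exponential failure: ln(0.92)/ln(0.83) = 0.447.
- Freedman events: (1.960 + 1.282)² × [(1 + 0.447)/(1 − 0.447)]² gives 73 after rounding up. At 71 events the power is 89.5%.
- Expected events: with exponential attrition and follow-up spread evenly over 33 to 50 months, the event probabilities are 0.1591 and 0.0752. Then 623/2 × (0.1591 + 0.0752) = 73.0.

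So 623 participants and about 71 events are reproduced from 83% v 92%. The printed hazard ratio of 0.42 differs from 0.447. That is a separate matter, and the simulation below is calibrated to the two percentages.

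**3. Effect of adding a covariate.** The prognostic strength is an assumption. Simulation of 1,500 trials per row: N = 623, marginal three-year vitality 83% v 92%, attrition and follow-up as above, and a Cox model with and without one standardised covariate.

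| Assumed HR per SD | Power without | Power with | Difference (points) |
|---|---|---|---|
| 1.0 | 92.6% | 92.6% | 0.0 |
| 1.25 | 91.3% | 91.6% | 0.3 |
| 1.5 | 91.3% | 92.0% | 0.7 |
| 2.0 | 91.1% | 93.4% | 2.3 |
| 2.5 | 91.3% | 95.0% | 3.7 |
| 3.0 | 90.9% | 94.9% | 4.0 |

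The Monte Carlo standard error of each power is about 0.7 points.

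**4. Where the gain comes from.** At HR 2.0 per SD the average treatment hazard ratio moves from 0.445 to 0.432, and the mean standard error from 0.2544 to 0.2550. The ratio of log hazard ratio to standard error goes from 0.8086/0.2544 = 3.18 to 0.8403/0.2550 = 3.30. The squared ratio of the unrounded values is about 1.07, a gain in information of about 7%, or roughly 0.07 × 623 = 44 participants. A second simulation of 2,000 trials per strength gave about 3%, 7% and 16% at HR 1.5, 2.0 and 2.5.

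**5. Chance imbalance.** In that second simulation, the adjusted and unadjusted log hazard ratios differed with a standard deviation of 0.04 to 0.09. The standard error of the log hazard ratio is about 2/√71 = 0.24, so the shift is about 0.04/0.24 = 17% to 0.09/0.24 = 38% of one standard error.

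**6. Limits.** The comparison model in the simulation had no covariates and no clinician effect. If the minimisation factors already carry part of the prognostic information, the gain is smaller. The pulp-exposure model was not simulated.

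**The case against.** The other side is largely right, and three stronger readings should be set aside.

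**That the protocol itself treats these variables as strong drivers of failure.** A reader might infer this from the threefold factor (6.6% × 3 = 19.8%). But that factor is a planning estimate that contrasts teeth of every depth with pulpal-third teeth, and the inclusion criteria admit only the latter. Eligibility therefore removes most of the contrast. Some variation is left: the Background describes the five-year stepwise trial as treating pulpal-quarter lesions in patients with more severe caries, and the sample size section again calls those lesions deeper. The pulpal quarter lies inside the pulpal third, so the authors do regard depth within the eligible range as relevant to outcome. They give no size for it. For age there is even less: it appears only as an exploratory effect modifier, which is not a statement about prognosis.

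**That the omission biases the result.** It does not. Prespecified adjustment for the minimisation factors is a valid analysis of a randomised trial. Chance imbalance is part of the sampling error that the confidence interval already reflects. The move from 0.445 to 0.432 is the difference between a marginal and a conditional hazard ratio, not an error.

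**That the change is free.** It is nearly so. No scale for extent is defined, films come from routine care, and no rate of missing films is given.

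It can also be said that covariates belong in the analysis plan, which is not shown and may already include these. That is fair. Still, the article does state a covariate set for both models, so a suggestion to extend it addresses stated text and does not complain of missing detail.

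**Conclusion.** The point stands as an optional improvement. Both models name the minimisation covariates and no others, and two usable pre-treatment variables are left out. The planned analysis is sound and no stated sample-size figure changes.

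Over assumed hazard ratios of 1.0 to 3.0 per SD the gain is about 0 to 4 points of power. Up to 1.5 it is under 1 point, within the simulation's own precision; gains of 2 points or more appear only from 2.0 upwards. The documents do not say where in that range age or residual depth lies. If neither is prognostic, nothing is gained and power is not reduced (92.6% both ways). The case is better for caries extent than for age, because only depth has any support in the text.

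**What to change.** Before any outcome data are seen, add a sentence to the statistical analysis plan: the Cox model for sustained tooth vitality and the logistic model for pulp exposure will also include, as fixed covariates, age (continuous) and caries extent from the masked reading of the pre-treatment radiograph, on whatever scale the reader uses.

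- Take extent from the pre-treatment film alone. Do not use the clinician's baseline clinical entry, which is recorded after treatment (Identifying and recruiting participants) and so could be influenced by it.
- Use simple imputation for missing readings, for example the overall mean computed without regard to arm.
- Report the model with minimisation covariates only as a sensitivity analysis.

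The cost is wording, with no new data collection. The small downsides are two or so extra parameters with about 71 events, some imputation for missing films, and a hazard ratio that is conditional on more covariates.
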